## 3. Statistical analysis

### 3.1 Behavioral data

Analysis will be performed according to the *intention to treat principle*. Differences in scores on each of the dependent variables will be examined for T1-T3. The significance of possible differences will be tested with logistic multilevel modeling [54] with the condition (REFLEX or Control) and treatment phase (T1-T3) as levels. A model will be built for each of the dependent variables. Dummy variables will be created for each level and the statistical significance of the regression effects will be tested using the approximate t-test. The dummy variables and their interaction are entered as fixed effects in the model. As random effects, the between-individual and within-individual variance were estimated. All models will be built using the program MlwiN.

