### 2.3 Sample size calculation

A previous study on a treatment to improve insight in schizophrenia [42] observed a mean effect size of 0.51 (standardized mean difference). We used this effect size for our power analysis. Sample size was computed using the program developed by [name] (Harvard School of Public Health) http://hedwig.mgh.harvard.edu/biostatistics/software.Using the estimated effect size of 0.51, this yielded a total number of 128 patients, with a power of 0.80.

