##### Self-reflection

*The Self-Reflection and Insight Scale *[46] is a self-rating questionnaire consisting of the factors 'Need for self-reflection', 'Engagement in Self-reflection' and 'Insight'. The scale consists of 20 Likert-scale items.

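### Section 3.1 names a logistic multilevel model for every behavioural outcome, but the outcomes are scale scores with no binary endpoint, and the section's other statements and the sample size imply a linear model

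*Protocol article*

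**What the plan says.** Section 3.1 gives one model type for the behavioural data. Differences will be "tested with logistic multilevel modeling [54] with the condition (REFLEX or Control) and treatment phase (T1-T3) as levels", and the model applies to every outcome: "A model will be built for each of the dependent variables".

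The same section describes the rest of the analysis as follows:
- Object of the comparison: "Differences in scores on each of the dependent variables will be examined for T1-T3".
- Fixed part: "The dummy variables and their interaction are entered as fixed effects in the model".
- Random part: "As random effects, the between-individual and within-individual variance were estimated".
- Test: "the statistical significance of the regression effects will be tested using the approximate t-test".

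The primary measures in section 2.4.3.1 are the ISMI (29 Likert items), the BCIS (one subscale score minus another), the Self-Reflection and Insight Scale ("The scale consists of 20 Likert-scale items") and the six-item Theory of Mind subscale of the DACOBS. Section 2.3 rests the sample size of 128 on an earlier study that "observed a mean effect size of 0.51 (standardized mean difference").

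**The concern.** A binary logistic model describes the log-odds of an event. The article defines no event for any outcome. Its only cut-offs, on the Psychosis Insight Scale and on PANSS item G12 in section 2.2, decide eligibility.

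This is the only model named for the primary and secondary behavioural outcomes. Taken at its word, it leaves open whether the treatment effect will be a mean difference, an odds ratio at an unstated cut, or a cumulative odds ratio. Those are different effect measures with different power, and only the first matches the basis of the sample size.

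**Working it through.** **Step 1: set the statements side by side.**

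| Statement in the article | Model it fits |
|---|---|
| Logistic multilevel model (3.1) | Binary or ordinal outcome |
| Differences in scores are examined (3.1) | Linear |
| Variance within individuals is estimated (3.1) | Linear; in a standard binary logistic model the distribution fixes the occasion-level variance |
| Condition and phase dummies with interaction as fixed effects (3.1) | Either |
| Approximate t-test of regression effects (3.1) | Either |
| Multi-item totals or a difference of subscale scores (2.4.3.1) | Linear |
| Standardized mean difference of 0.51 (2.3) | Linear |

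Only the word *logistic* points away from a linear model.

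**Step 2: reproduce the sample size.** Inputs from section 2.3 are d = 0.51, power 0.80 and N = 128. Allocation is taken as 1:1 from the balanced blocks in section 2.5. The significance level is not stated, so two-sided 5% is assumed.

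- Normal approximation: n per arm = 2(1.960 + 0.842)² / 0.51² = 60.4, rounded up to 61, so 122 in total. The exact t-test gives 124.
- d = 0.50 with the t-test gives exactly 128, so the stated figure is slightly conservative for 0.51.
- Power with 64 per arm and d = 0.51: the noncentrality is 0.51 × √(64/2) = 2.885. The normal approximation gives Φ(2.885 − 1.960) = 0.82, and the t-test gives 0.817.

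The claim of 0.80 power therefore stands for a linear comparison of means.

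**Step 3: what a binary endpoint would cost, if one were intended.** Assumptions: normal scores with equal SD, a single time point, no dropout and no clustering.

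The asymptotic efficiency of a cut at quantile q is φ(z_q)² / [q(1 − q)]. At the median this is 2/π = 0.637, and 128 × 0.637 = 81.5 patients' worth of information. The t-test power with 40.7 per arm is 0.623. Efficiency is 0.622 at the 60th percentile, 0.576 at the 70th, 0.490 at the 80th and 0.342 at the 90th.

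The same check through two proportions p₁ and p₂, with mean p̄ and n = 64 per arm, uses power = Φ{[|p₁ − p₂|√n − 1.960√(2p̄(1 − p̄))] / √(p₁(1 − p₁) + p₂(1 − p₂))}:

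| Controls above cut | REFLEX above cut | Power at N = 128 | Total N for 80% power |
|---|---|---|---|
| 39.9% (cut midway between arm means) | 60.1% | 0.627 | 192 |
| 50% | 69.5% | 0.616 | 198 |
| 30% | 49.4% | 0.615 | 198 |
| 20% | 37.0% | 0.569 | 220 |
| 10% | 22.0% | 0.457 | 290 |

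**The case against.** The strongest reply is that *logistic* is a slip for *linear*. The comparison of scores, the two variance components and the mean-difference sample size all point to a linear mixed model, which can be fitted to these data. On that reading the loss of power is nil. This reply largely stands as an account of what was probably meant. It does not remove the error: the evidence that the word is a slip is the same evidence that the named model is wrong.

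A reader might go further in four ways that the article does not support:
- *The primary analysis either cannot be fitted or forces dichotomised outcomes.* This is not exhaustive. Section 3.1 itself describes a linear model that can be fitted, and an ordinal logit model is another possibility, notably for the seven-point item G12.
- *The plan loses about a third of its information.* No dichotomisation is planned. The loss of 1 − 0.637 = 36% belongs to a hypothetical median split of a normal score.
- *Calling condition and phase levels makes the hierarchy wrong.* The wording is loose, but the section then enters both as fixed-effect dummies and gives the random part separately as variance between and within individuals.
- *Cut-points would be chosen after the data are seen.* The article mentions no outcome cut-points, and any that exist could be in documents not shown here.

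**Conclusion.** The point holds as an internal contradiction about the main analysis model. Section 3.1 names a logistic model for outcomes that are scores, against its own description of the comparison and the variance components, and against section 2.3. As written the model name is wrong and should be corrected, because it is the only model given for all primary behavioural outcomes.

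The size depends on what is meant. If linear, power at N = 128 and d = 0.51 is about 0.82 and only the text is at fault. If binary endpoints are truly intended, power is about 0.62 to 0.63 for central cuts and falls to 0.46 with 10% of controls above the cut; 80% power would need 192 to 198 patients for central cuts and up to 290 for that extreme one. The binary figures rest on the assumptions in the working, including a two-sided 5% level that the article does not state.

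**What to change.** In section 3.1, replace the logistic model by a linear multilevel (mixed) model for all scale scores. State that measurement occasions are nested in patients, that condition, phase and their interaction are fixed effects, and that results are reported as mean differences with 95% confidence intervals. An ordinal model is an option for the single item G12.

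This costs one sentence. The fixed and random parts already described can stay, and the sample size is unaffected.

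If binary endpoints are intended after all, define each cut-point before the analysis and restate the power or the sample size in section 2.3. That would be a substantive change.

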### Research aims

Main aim of the study is to evaluate the efficacy of REFLEX. Primary outcome measures in this evaluation are the preconditions of insight as specified by our model, while insight is the secondary outcome measure of our trial. Effects of REFLEX on quality of life, self-esteem and mood will be examined as well.

An additional aim of the trial is to examine whether participation in REFLEX will lead to haemodynamic changes, blood oxygenation levels as measured by functional Magnetic Resonance imaging (fMRI), during perspective-taking and self-reflection.

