#### 2.4.3 Assessment

##### 2.4.3.1 Behavioral measures

##### Primary outcome measures (preconditions of insight)

As REFLEX aims to improve insight via improving its preconditions, preconditions of insight according to our model are the trials primary outcome measures.

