##### Internalized stigma

*The Internalized Stigma of Mental Illness Scale *(ISMI;[45] is a self-rating questionnaire designed to measure the subjective experience of stigma, with subscales measuring Alienation, Stereotype Endorsement, Perceived Discrimination, Social Withdrawal and Stigma Resistance. The ISMI was developed in collaboration with people with mental illnesses and contains 29 Likert items.

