##### Self-reflection and mental flexibility

*The Beck Cognitive Insight Scale *(BCIS; [6]) is a self-rating questionnaire developed to evaluate patients' self-reflectiveness and idiosyncratic self-certainty (the ability to consider other possibilities than one's own opinion). The scale consists of 15-items, divided into two subscales: a 9-item self-reflectiveness subscale and a 6-item self-certainty subscale. Total scores are obtained by subtracting the score of the self-certainty subscale from the score on the self-reflectiveness subscale.

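### Four unranked primary instruments, each tested at two follow-up times, have no stated deciding contrast, time point or success rule, while the sample size fits a single comparison

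*Protocol article*

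**What the plan says.** Research aims: "Primary outcome measures in this evaluation are the preconditions of insight as specified by our model". The opening of the primary outcome section repeats this: "preconditions of insight according to our model are the trials primary outcome measures". Neither place ranks them.

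Four instruments follow under that heading:
- ISMI, which "is a self-rating questionnaire designed to measure the subjective experience of stigma"; five subscales are listed.
- BCIS, "divided into two subscales: a 9-item self-reflectiveness subscale and a 6-item self-certainty subscale", with a total score defined as the difference between the two.
- The Self-Reflection and Insight Scale, which "is a self-rating questionnaire consisting of the factors" need for self-reflection, engagement in self-reflection and insight. No total score is described.
- The Theory of Mind subscale of the DACOBS.

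BCIS appears again under the secondary outcome measures, as a measure of insight.

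Section 2.5 sets assessments before training (T1), directly after (T2) and six months after (T3). Section 3.1 states "A model will be built for each of the dependent variables", with dummies for condition and phase and their interaction as fixed effects, and adds that "the statistical significance of the regression effects will be tested using the approximate t-test".

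Section 2.3 takes one standardised effect of 0.51 from an earlier study of a treatment for insight, and "this yielded a total number of 128 patients, with a power of 0.80". It does not tie the calculation to any of the four instruments.

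**The concern.** A reader cannot tell from the article which result would show that REFLEX works. Four instruments at two follow-up times give eight condition-by-phase terms, and all of them fall under the same instruction to test the regression effects. The duplicate listing of BCIS leaves even the membership of the primary set open.

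The two natural success rules fail in opposite directions. If one positive result among eight is enough, the chance of a false claim of efficacy is well above the level of a single test. If every instrument must be positive, the false-positive rate is controlled but the stated power no longer describes the trial. The sample size works for neither rule.

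**Working it through.** **Inputs**
- Four primary instruments (primary outcome section); follow-up at T2 and T3 (section 2.5). Condition-by-phase terms: 4 × 2 = 8.
- d = 0.51, N = 128, power 0.80 (section 2.3). Allocation is taken as 1:1, 64 per arm, since section 2.5 describes balanced blocks.
- Alpha is not stated. Two-sided 0.05 is an assumption, checked in step 1.
- Correlation between instruments is not given; 0 to 0.7 is tried.

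**1. The plan's own figure.** Two-sample t-test, two-sided 0.05, power 0.80:
- d = 0.51 needs N = 124; d = 0.50 needs N = 128.
- 64 per arm at d = 0.51 gives power 0.817.
- A one-sided 0.05 test at d = 0.51 needs only 98.

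So 128 fits one two-sided 5% comparison, apparently with the effect rounded to 0.50. It leaves no allowance for several primary tests.

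**2. Correlation between the two time contrasts.** Section 3.1 models a between-individual and a within-individual variance. With within-individual variance σ² and complete data, T2−T1 and T3−T1 each have variance 2σ² and share the T1 error, so their covariance is σ². The correlation is σ² / 2σ² = 0.5.

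**3. Error if any one result counts.** Independent tests: 1 − 0.95⁴ = 18.5%; 1 − 0.95⁸ = 33.7%. The correlated cases come from simulated normal test statistics with time correlation 0.5. The correlation between different instruments at different times is set to the product of the two correlations.

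| Between-instrument correlation | 8 tests | 4 tests (one per instrument) |
|---|---|---|
| 0 | 31.7% | 18.5% |
| 0.3 | 29.8% | 17.4% |
| 0.5 | 26.9% | 15.6% |
| 0.7 | 22.7% | 13.0% |

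**4. Power if all four must succeed at one time point.** With d = 0.51 on every instrument, 64 per arm and no dropout:
- Independent instruments: 0.817⁴ = 0.445, or about 0.46 by the normal approximation.
- Between-instrument correlation 0.7: 0.64 by t-test power, 0.65 by the normal approximation.

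The range is about 0.45 to 0.65.

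**5. Power under a correction across four instruments.** The first Holm step uses 0.05 / 4 = 0.0125. At 64 per arm and d = 0.51, t-test power is 0.637. Restoring 0.80 at that threshold needs about 176 patients.

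Steps 4 and 5 treat 0.51 as the standardised effect on whichever contrast is tested. The source study concerned insight, which is a secondary outcome here, so applying 0.51 to each precondition is itself an assumption.

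**The case against.** The strongest defence is that this is a condensed journal article. Alpha and the method of multiplicity adjustment commonly sit in the full protocol or the analysis plan, neither of which is shown. That stands. A reader might infer that the plan tests everything at an unadjusted 5%, but the article states no alpha and does not rule out an adjustment. The absence of an adjustment method is not the point made here.

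A second defence is that the error rates in step 3 depend on an any-one-is-enough rule that the article never states. The preconditions are distinct parts of a model, partly addressed by different modules, so a separate conclusion for each is a possible reading. This also stands, and it is why the figures are conditional and the all-must-succeed case is shown beside them.

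Two stronger readings should not be drawn:
- A reader might count 11 subscales at two times, giving 22 tests and 1 − 0.95²² = 67.6%. The subscales are mentioned to describe the questionnaires, and nothing makes each one a dependent variable.
- A reader might object that a significant condition term would be only a baseline difference. That is true if T1 is the reference phase, but the coding is not given, nothing says that term will count as evidence of efficacy, and the relevant interaction is in the model.

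What the defences do not remove is that the article itself sets out the primary outcomes, the models and the sample size. Together these give several hypotheses, sample size for one, and an instrument in two tiers.

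**Conclusion.** The point holds in conditional form. The unranked primary set, the missing deciding contrast, time point and success rule, and the double listing of BCIS can all be read directly from the article. The sizes depend on how success is defined, and neither definition agrees with a 5% error rate and 0.80 power together:
- Any one of eight results: error about 23% to 32%, with 34% the independence figure. With one test per instrument, about 13% to 18.5%.
- All four at one time point: power about 0.45 to 0.65.

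The assumptions are a two-sided 5% level inferred from N = 128, equal arms, complete data, between-instrument correlation of 0 to 0.7, and d = 0.51 on every instrument. The choice of outcome, contrast and time point determines the sample size, so it belongs in the protocol and cannot be left as analysis detail.

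**What to change.** Before any unblinded results are seen:
1. In section 3.1, name the condition-by-phase interaction at one prespecified time point as the efficacy test. Whether that is T2 or T3 is the sponsor's decision; the article gives no ground for preferring either.
2. Fix one score per instrument. This matters most for the Self-Reflection and Insight Scale, which has three factors, one of them called insight, and no total defined.
3. Assign BCIS to one tier. If it becomes secondary only, mental flexibility has no primary measure left, and the text should acknowledge that.
4. Then either name one instrument primary, or test the primary instruments with Holm at family-wise two-sided 0.05.
5. State alpha in section 2.3 and restate power for the chosen option.
6. Report the other time point, the subscales and the remaining outcomes as supportive, with confidence intervals.

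In text this costs about a paragraph. A single primary instrument keeps power at about 0.80 but allows fewer confirmatory claims. Holm over four instruments keeps all four claims open, with power of about 0.64 per scale at the first step (128 patients, d = 0.51, no dropout).

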### 2.5 Procedure

Patients who fulfill the inclusion criteria, will be invited to participate in the study. If a patient is willing to participate, study procedures will be explained in detail and after a period of two weeks written informed consent is obtained. Subsequently, diagnosis is verified by the Mini Plus, a semi-structured interview to assess DSM IV pathology [53]. Thereafter, patients are randomly allocated to REFLEX or control condition. Randomization procedures start when the required number of patients per center (ranging from 17-19) are included, or when the first patients was included more than six weeks ago while >10 people are included.

Randomization is centrally coordinated by the Trial Coordination Center of the University Medical Hospital Groningen. The project coordinator gives the subject a unique code and these codes are entered for each patient into a computerized systematic program by an independent researcher. Results of the randomization process are passed to the project coordinator in sealed envelopes and distributed to the on-site therapists. Subsequent subjects are randomized in blocks of two or four, to ensure that the number of patients will be balanced over conditions. Assessment takes place before (T1), directly after (T2) and six months after the training (T3). Assessors are not aware of the condition (control or treatment) the subject is in. During the entire trial patients receive treatment as usual, with the exception of cognitive behavioral therapy.

All fMRI scans will be made in the Neuroimaging Center of the UMCG in Groningen, right before (T1) and directly after (T2) treatment. For geographical reasons, recruitment for the fMRI study is limited to the institutions located in the North of the Netherlands: GGZ Drenthe, Assen; UMCG and Lentis, Groningen, and GGZ Friesland, Leeuwarden. Patients who participate in the fMRI study will be randomized separately.

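### The planned model leaves T1 free in each arm and fits one common correlation: an unbiased effect estimate that is less precise than T1 allows, with standard errors that are right only if T1, T2 and T3 are equally correlated and equally variable

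*Protocol article*

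**What the plan says.** Section 3.1 (Behavioral data) says that differences are to be "tested with logistic multilevel modeling [54] with the condition (REFLEX or Control) and treatment phase (T1-T3) as levels". One model is built per dependent variable. On the fixed part: "The dummy variables and their interaction are entered as fixed effects in the model". On the random part: "As random effects, the between-individual and within-individual variance were estimated". On testing: "Dummy variables will be created for each level and the statistical significance of the regression effects will be tested using the approximate t-test". It mentions no T1 covariate, no equal-baseline constraint and no robust standard error.

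Section 2.5 (Procedure) gives the timing: "Assessment takes place before (T1), directly after (T2) and six months after the training (T3". On allocation it says: "Subsequent subjects are randomized in blocks of two or four, to ensure that the number of patients will be balanced over conditions".

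Section 2.3 (Sample size calculation) gives the power statement: "Using the estimated effect size of 0.51, this yielded a total number of 128 patients, with a power of 0.80". It states no alpha, no sidedness and no correlation between repeated measurements.

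**The concern.** The point concerns what the article specifies, in two parts.

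**Fixed part.** With condition, phase and their interaction all free, the condition dummy estimates a separate T1 mean in each arm. Each interaction term is then a difference between arms in mean change from T1. Randomisation makes the T1 means equal in expectation, so estimating a T1 difference gives up information that the trial already collects. If the correlation with T1 is low, the contrast is even less precise than a comparison that ignores T1.

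**Random part.** One between-person and one within-person variance amount to a random intercept. This forces the T1-T2, T1-T3 and T2-T3 correlations to be the same and the variances to be equal. T3 is six months after training, so the T1-T3 correlation may well be lower than the others. The tests use model-based standard errors, so a wrong covariance would pass straight into the p-values of every outcome.

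**Working it through.** **Inputs.** Standardised difference 0.51, 128 patients and power 0.80 (section 2.3). Equal allocation, 64 per arm (from the balanced blocks in section 2.5). Assumed because not stated: two-sided alpha 0.05, complete data, equal variances across phases, 0.51 expressed in SD units of the outcome, and all correlations.

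**The plan's own figure.** A two-sample t-test with 64 per arm and d = 0.51 has power 0.817 (0.823 by the normal approximation). The required total is 124 by the t-test and 122 by the normal approximation; d = 0.50 with the t-test gives exactly 128. The stated power of 0.80 is reproduced closely enough, and it is not in dispute here.

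**Precision.** With outcome variance 1 and correlation rho between T1 and the follow-up:

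- T1 free: contrast variance proportional to 2(1-rho).
- T1 means constrained equal, or T1 as covariate: proportional to 1-rho².
- Ratio: (1-rho)(1+rho) / [2(1-rho)] = (1+rho)/2, so the saving is (1-rho)/2.

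Power uses the noncentral t with effect 0.51/√variance and 64 per arm.

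| rho (assumed) | T1 free | T1 used | Saving | Power, T1 free | Power, T1 used |
|---|---|---|---|---|---|
| 0.3 | 1.40 | 0.91 | 35% | 0.68 | 0.85 |
| 0.5 | 1.00 | 0.75 | 25% | 0.82 | 0.91 |
| 0.7 | 0.60 | 0.51 | 15% | 0.96 | 0.98 |

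The saving is 40% at rho 0.2 and 5% at rho 0.9. A generalised least squares calculation with 64 per arm and three time points gives the same 35%, 25% and 15%. At rho = 0.5 the T1-free variance is 1, the same as ignoring T1. The planned contrast drops below power 0.80 when rho is below about 0.48.

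**Standard errors.** With complete data and equal variances, the random-intercept model estimates the residual variance as w = 1 - mean(r12, r13, r23). It uses 2w for both change contrasts. The true values are 2(1-r12) at T2 and 2(1-r13) at T3. The ratio of model to true standard error is therefore √[w/(1-r12)] at T2 and √[w/(1-r13)] at T3. Type I error is 2[1-Φ(1.96 x ratio)].

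| r12, r13, r23 (assumed) | w | T2 ratio | T2 type I | T3 ratio | T3 type I |
|---|---|---|---|---|---|
| 0.5, 0.5, 0.5 | 0.500 | 1.00 | 5.0% | 1.00 | 5.0% |
| 0.6, 0.5, 0.6 | 0.433 | 1.04 | 4.1% | 0.93 | 6.8% |
| 0.7, 0.5, 0.6 | 0.400 | 1.15 | 2.4% | 0.89 | 8.0% |
| 0.7, 0.49, 0.7 | 0.370 | 1.11 | 3.0% | 0.85 | 9.5% |
| 0.5, 0.25, 0.5 | 0.583 | 1.08 | 3.4% | 0.88 | 8.4% |
| 0.6, 0.5, 0.7 | 0.400 | 1.00 | 5.0% | 0.89 | 8.0% |
| 0.6, 0.5, 0.8 | 0.367 | 0.96 | 6.1% | 0.86 | 9.3% |

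The T3 standard error is too small whenever r13 is below the mean of the three correlations. The T2 standard error is too large only if r12 exceeds (r13+r23)/2. In the sixth row it is exactly right, and in the last row it is too small.

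**The case against.** Leaving T1 free is a standard model and is unbiased under randomisation. At rho of 0.5 or more it meets the stated power of 0.80 as it stands. This is correct: the first part is lost precision, not an error of validity.

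Every figure needs a linear model, while section 3.1 says 'logistic'. That also stands, and the wording has to be settled first. Linear is the sensible reading, because the outcomes are scale scores and a within-person variance is to be estimated.

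Covariance detail is often left to a fuller document. Here, however, the article names its random terms, and the two it names imply a common correlation. It does not use the term compound symmetry, so a fuller plan could clarify the point.

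The constraint is safe only if T1 scores cannot be affected by knowledge of allocation. Section 2.5 places T1 before training without saying that it precedes allocation. This is a fair condition on the fix.

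Three stronger readings are tempting, and the documents support none of them:

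- A reader might infer that 15-35% of the achievable variance reduction is thrown away. Those percentages are the fall in the contrast variance itself at assumed rho 0.7 to 0.3. Measured against rho², the reduction achievable relative to a follow-up-only comparison, the share lost is 18% at rho 0.7 and 100% at rho 0.5.
- A reader might infer that the standard errors are wrong. They are right if correlations and variances are equal, and the article gives no values for either.
- A reader might infer that T3 rejects too often and T2 too rarely. The T2 direction is not general, as the last two rows of the second table show.

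**Conclusion.** The point holds as a nearly free gain in precision, plus a conditional risk to the standard errors. For any rho below 1, using T1 lowers the variance of the treatment contrast by (1-rho)/2. Power falls short of the stated 0.80 only if rho is somewhat below 0.5, and only if 0.51 is in outcome-SD units; section 2.3 says no more than that it is a standardised mean difference. If the T1-T3 correlation is below the average of the three, the T3 test is anticonservative: 6.8% to 9.5% instead of 5% in the patterns tried. No general statement can be made for T2. All of this rests on a linear reading, complete data, two-sided alpha 0.05 and assumed correlations.

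**What to change.** Correct 'logistic' to linear. Then either constrain the T1 means to be equal (phase dummies plus condition x T2 and condition x T3, without a condition main effect) or model T2 and T3 with T1 as covariate. In place of the single random intercept, use an unstructured within-patient covariance: 3 x 3 with T1 as an outcome, 2 x 2 if T1 is a covariate.

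The cost is mainly specification. The 3 x 3 form has six covariance parameters instead of two, which 128 patients can support. There is also one procedural condition: confirm, and state in section 2.5, that the T1 measures are completed before allocation is made known to patients. This matters because the section 2.4 measures listed as primary are self-ratings.
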